##### Implementation fidelity

Prior to measuring the effectiveness of the intervention on patient and health services outcomes, the implementation strategy requires evaluation. This evaluation will focus on implementation fidelity, where the extent to which an intervention is delivered per the intended implementation plan is measured [52, 53]. Evaluation of our behaviour-change-informed strategy will be developed using the RE-AIM Scoring Instrument and measured using data from (i) the post HIRAID® implementation nurse survey, (ii) HIRAID® Facilitator surveys, and (iii) documentation audits.HIRAID® Inpatient Facilitator survey. Facilitators will independently complete intervention fidelity scoring, that asks to what degree the behaviour change mechanisms were implemented [53, 54]. Implementation scores range from 0 (“not implemented”) to 2 (“fully implemented”). Adaptions for each mechanism will be scored from 1 (“just as planned”) to 4 (“many changes from plan”) [55].

#### Statistical methods

##### HIRAID® effectiveness/clinical outcomes

Survey and health record data collected for implementation evaluation will be analysed using descriptive statistics to assess fidelity levels and feedback from study sites. Descriptive statistics will be calculated using the chi-square test for categorical variables, and the *T*-test (normally distributed data) or the Mann-Whitney *U* test (non-normally distributed data) for continuous variables. All analyses will follow the intention-to-treat principle, with all clusters evaluated according to their original group allocation, regardless of adherence or protocol deviations. Comparisons within and across clusters will be conducted using the generalised linear mixed model (GLMM) approach, applying appropriate link functions tailored to each outcome variable. For binary outcome measures, a GLMM with a binary logistic link function will be used, while for count outcome measures, GLMMs with Poisson or negative binomial link functions will be applied. The model will account for the random effect of the cluster and will adjust for relevant confounders, identified in the descriptive analyses, as fixed effects. SPSS V28™ (IBM Corp., Armonk, NY, USA) will be used and the alpha set to < 0.05 [18].

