### Phase 3: Implementation evaluation of HIRAID® Inpatient

#### Study design

In Phase 3, the HIRAID® Inpatient framework will be implemented using a Type II effectiveness-implementation hybrid design [29], including a SW-cRCT [30]. The hybrid approach allows testing of the implementation strategy at the same time as observing the outcomes of the intervention [29, 30]. Four clusters will be progressed through three sequential phases: control, intervention transition and post-intervention, with a staggered rollout and a 1:1 allocation ratio, with most data collected from each defined population as outlined in Table 4. The trial is structured within a superiority framework, aiming to demonstrate improved outcomes compared to usual care.

Each participating hospital ward (cluster) will begin in the control phase, representing a period of routine or usual care before the scheduled implementation of the HIRAID® Inpatient framework. During this phase, baseline data and behavioural diagnostics will be collected to serve as the comparator for the intervention. Rather than using a separate, concurrent control group, this SW-cRCT uses each cluster as its own control. Data gathered during the pre-intervention phase will be directly compared with data collected post-implementation. This design enables evaluation of the intervention against established, real-world clinical practice. The HIRAID® Inpatient intervention will then be implemented over a three-month period (Intervention Transition), followed by an intervention data collection period, lasting between 3 and 12 months, depending on the cluster (Fig. 3).

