**Fig. 3 Fig3:**
[figure not shown]
The stepped-wedge cluster randomised controlled trial design for the implementation of HIRAID® Inpatient across four clusters. Each sequence comprises a 3- to 12-month baseline control condition, a 3-month intervention transition period, and a 3- to 12-month intervention exposure condition

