#### Randomisation

Each cluster will be randomly allocated to one of four starting dates for implementation. Randomisation will be performed by the study statistician using computer-generated numbers. Participating wards will have no influence over the allocation prior to randomisation, ensuring concealment of the allocation sequence until wards are assigned. No further changes to clusters will be made once the allocation has been finalised to minimise the risk of bias.

We are unable to randomise sites to clusters because of geographical location and clinical governance. The significant geographical distance between sites, mitigates the risk of contamination due to reduced proximity. Randomising clusters based on health service provides consistent clinical governance for study operations.

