#### Sample size

Sample sizes were calculated for each of the hypotheses. Hypotheses H1, H2, H3, and H6 sample size estimations were conducted collectively, as they will use medical record and cost data from relevant systems for the period of 1 st July 2026 to 1 st December 2027 (Table 4—shaded grey). To maximise the study’s power in detecting true differences, should they exist, the largest sample size estimation is reported and will be used. Sample sizes were calculated with an assumed intra-class correlation of 3%, 5% significance (two-tailed) and 80% power, and applying Woertman’s SW design estimate approach [48]. These sample sizes have been calculated using the most recent data from the study sites and/or previous work by the investigators in this field. To evaluate implementation fidelity HIRAID® facilitators (CNCs/CNEs) employed to assist with education and roll out will be invited to participate in the evaluation of implementation fidelity. The number of staff to be involved in this process will be determined by each LHD.

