### Trial status

All ethical and governance approvals are in place at participating hospitals. The protocol is Version 5.0 dated 30th April 2025. Recruitment is scheduled to begin on the first of July 2026 and will be completed approximately on 31 st December 2027. The trial is prospectively registered with the Australia New Zealand Clinical Trial Registry ACTRN12625000639426 (registration date: 17/06/2025).

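### The Phase 3 effectiveness model does not commit to calendar-period adjustment and the design section describes a direct pre-post contrast, so a steady background trend would pass almost in full into the effect estimate

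*Protocol article*

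**What the plan says.** The model is set out in the protocol article, Phase 3, Statistical methods, under HIRAID® effectiveness/clinical outcomes: "Comparisons within and across clusters will be conducted using the generalised linear mixed model (GLMM) approach", with link functions suited to each outcome. Its adjustment terms are given as: "The model will account for the random effect of the cluster and will adjust for relevant confounders, identified in the descriptive analyses". Calendar time, period and season are not mentioned. Table 3 lists descriptive methods, GLM, and linear and logistic regression, also without a time term.

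Phase 3, Study design, describes the contrast: "Rather than using a separate, concurrent control group, this SW-cRCT uses each cluster as its own control", and then "Data gathered during the pre-intervention phase will be directly compared with data collected post-implementation".

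The layout comes from three places. Randomisation: "Each cluster will be randomly allocated to one of four starting dates for implementation". Fig. 3 caption: "Each sequence comprises a 3- to 12-month baseline control condition, a 3-month intervention transition period, and a 3- to 12-month intervention exposure condition". Trial status: "Recruitment is scheduled to begin on the first of July 2026 and will be completed approximately on 31 st December 2027".

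The Sample size section names Woertman's stepped-wedge approach: "Sample sizes were calculated with an assumed intra-class correlation of 3%, 5% significance (two-tailed) and 80% power". The Study Plan section allows other initiatives during the trial and says they will be recorded. It states no adjustment for them.

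**The concern.** In a stepped wedge every cluster moves from control to intervention and never back, so exposure and calendar time rise together. The randomised start dates help separate the two only if the analysis compares clusters in different conditions at the same calendar time. Terms for period are the usual way to do this.

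A model with a random cluster effect and no time term mostly compares each cluster's later data with its own earlier data. Any drift in rapid response calling, complication coding, incident reporting or staffing is then partly or wholly read as an effect of HIRAID® Inpatient. The Study design sentences describe just such a contrast. The rate outcomes behind H1 to H3 are the most exposed, and the H2 target is only 10%.

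**Working it through.** The documents state no figure for this point, and Table 4 is not visible, so there is nothing to reproduce. The check asks how much of a time trend the described model would absorb.

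**1. Layout.** From the Fig. 3 caption and Trial status: 18 months from July 2026, six quarters, four sequences with one cluster each. Mid-points in months:

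| Sequence | Control | Intervention | Mid-point gap |
|---|---|---|---|
| 1 | 0–3 | 6–18 | 12.0 − 1.5 = 10.5 |
| 2 | 0–6 | 9–18 | 13.5 − 3.0 = 10.5 |
| 3 | 0–9 | 12–18 | 15.0 − 4.5 = 10.5 |
| 4 | 0–12 | 15–18 | 16.5 − 6.0 = 10.5 |

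The Sample size section ends the data on 1 December 2027. With a 17-month window the gap is 10.0 months, for example (6 + 17)/2 − 1.5 in sequence 1.

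**2. Trend carried over.** Generalised least squares on cluster-period means, random cluster effect, ICC 0.03, 3000 patients per cell: without period terms the effect absorbs 3.50 times the quarterly trend (10.5 months). Over ICC 0.001 to 0.03 and 10 to 3000 per cell, the range is 3.0 to 3.5 quarters. With fixed period effects it is 0.000 throughout, for a trend common to all clusters.

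**3. Apparent effect with no true effect.** The yearly declines d are assumptions. Apparent reduction = 1 − (1 − d)^(10.5/12) = 1 − (1 − d)^0.875:
- d = 2%: 1 − 0.98^0.875 = 1.8%
- d = 5%: 1 − 0.95^0.875 = 4.4%
- d = 10%: 1 − 0.90^0.875 = 8.8%

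A decline of about 11% per year would by itself produce the 10% target of H2.

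**4. False-positive rate.** Assume 530 events per condition, Poisson. This is roughly 834 beds, fully occupied, for 7.5 months (about 228 days) at 2.8 per 1000 patient days: 834 × 228 × 0.0028 ≈ 532. Full occupancy is assumed, and 2.8 is the mean of the Table 2 rates, which describe health services and not study wards. SE of the log rate ratio = √(2/530) = 0.061. Shift = 0.875 × ln(1 − d) / 0.061:
- 2%: 0.29 SE, two-sided rejection about 6%
- 5%: 0.73 SE, about 11%
- 10%: 1.50 SE, about 32%

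A Poisson simulation with Table 2 admissions, no true effect and a 2% fall per quarter (1000 runs each) gave type I error of 0.05, 0.09, 0.20 and 0.38 at assumed rates of 2, 5, 20 and 50 per 1000 admissions. With period terms it stayed at 0.04 to 0.06 in all scenarios run.

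**5. Season.** With large cells, the sequences get weights 0.2, 0.3, 0.3 and 0.2. For a rise in July–September (quarters 1 and 5), the intervention share minus the control share is −3/4, −1/6, +1/6 and −1/4. The weighted sum is −0.20. For a rise over April–September it is −0.10. So 10–20% of the seasonal log rate ratio is carried, in favour of the intervention; smaller cells carry less. For assumed winter ratios of 1.2, 1.5 and 2.0 the spurious reduction is 1.8%, 4.0% and 6.7% at 0.10, and 3.6%, 7.8% and 12.9% at 0.20.

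**6. Agreement with the sample-size approach.** Woertman design effect with k = 4 steps, one baseline and one measurement per step, ρ = 0.03, n per cell:

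[1 + ρ(kn + n − 1)] / [1 + ρ(kn/2 + n − 1)] × 3(1 − ρ) / [2(k − 1/k)]

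For n = 50: (8.47/5.47) × (2.91/7.5) = 0.601. The least-squares variance on the same layout, relative to individual randomisation, is 0.601 with period effects and 0.236 without. At n = 3000 the figures are 0.646, 0.646 and 0.242. This is the classic layout without a transition period.

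**7. Price of adjustment.** On the trial's layout (ICC 0.03, 3000 per cell) the variance is 0.000377 with period effects and 0.0000808 without. The ratio is 4.66, so the SE ratio is √4.66 = 2.16.

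**The case against.** The strongest reply is that silence is being read as exclusion. The text is a condensed journal article, and an analysis plan may exist. The quoted sentence is not a full list of terms: it does not name the intervention indicator either. The model is said to serve comparisons across clusters as well as within them, and calendar time could enter as a relevant confounder. Naming Woertman's approach even suggests that a period-adjusted analysis may be intended. Background also describes rates of deterioration and complications as static.

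Part of this stands. A reader might infer that the trial will be analysed as an uncontrolled before-after study, or that the model rules period out. The documents do not support that. They leave an opening for time but do not commit to it. A reader might also infer that every secular or seasonal change is counted in full. That holds nearly for a steady trend, but a winter rise is carried only to about 10–20%. Nor does the text say that confounders will be chosen by significance test, only that descriptive analyses will identify them.

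What does not stand is that this is mere detail for an analysis plan. The Study design section positively describes a direct pre-post comparison without concurrent controls, and a period-adjusted plan would contradict that wording. Confounders identified from the data are no commitment to a term that the design makes necessary.

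**Conclusion.** The concern holds in this form: the stated analysis does not commit to period adjustment, and Study design describes a contrast that is confounded with calendar time. Followed as written, it would carry about 10.5 months of any steady common trend into the effect (10.0 if data end on 1 December 2027; 9 to 10.5 over the ICC and cell sizes tried), plus part of any winter rise.

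The carry-over follows from the layout. The apparent reductions of 1.8%, 4.4% and 8.8% rest on assumed declines of 2%, 5% and 10% per year, and the false-positive rates of about 6%, 11% and 32% also on an assumed 530 events per condition. At 2% per year the inflation is slight. The calculations concern event rates; no bias was quantified for the survey outcomes under H4 and H5.

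The mismatch with the Woertman approach is real but was checked only on the layout without transition. It says nothing about whether the Table 4 numbers are adequate, since that table is not visible.

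**What to change.** - In HIRAID® effectiveness/clinical outcomes, name fixed effects for calendar period in the effectiveness models, in quarters to match the 3-month steps, and estimate the intervention effect conditional on them.
- In Phase 3, Study design, replace the direct-comparison sentence with one that describes a comparison conditional on period, and reword the sentence that sets concurrent control aside.
- Prespecify the adjustment covariates in place of identifying them from the descriptive analyses.
- Treat the H3 primary outcome separately. The study sites had 14 Harm Score 1 events in 2023, so about 14 × 15/12 = 17.5 would be expected over the 15 non-transition months per cluster. Use a linear or coarser time term, or report this outcome descriptively.

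This changes wording only, and recruitment is not due to start until July 2026. The price is precision: an SE about 2.2 times that of the model without period. As an illustration, at an assumed 20 events per 1000 admissions, simulated power for a 20% reduction falls from about 0.90 to about 0.33; this ignores cluster-by-period variation. With so large a gap between the two models, the choice should be fixed before data are seen.

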*Descriptive approach—means and standard deviation for continuous variables, and frequencies and percentages for categorical variables. Cluster comparisons—ANOVA for continuous variables; Pearson’s Chi-Square tests for categorical variables

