#### Data collection

Several outcome measures will be collected from a variety of data sources during the control and intervention periods to evaluate the effectiveness of HIRAID® Inpatient and address the study hypotheses. Data will be collected from the patient health records made available by each ward, from patients, carers of patients, nurses, medical staff and the nurse facilitators who are employed to deliver the HIRAID® Inpatient training. Data collected on patient experience, record reviews, and staff surveys will be collected and directly entered into REDcap™ (Research Electronic Data Capture) (https://catalyst.harvard.edu/services/redcap/), a secure web-based application for data management and survey tool, managed by the University of Sydney. The type of data that will be collected from each of these sources, and when they will be collected, are summarised below and in Table 5.

**Table 5 Tab5:** Summary of the data to be collected from each population at pre- and post-intervention, and the instrument that will be used

Population	Pre-intervention (baseline)	Post-intervention (outcomes)	Instrument
Nurses	Behavioural diagnostics		Theoretical domain framework, focus groups
		HIRAID® Inpatient evaluation and feedback	Feedback survey
	Satisfaction with communication and handover		Satisfaction with communication survey
	Perception of factors that influence nursing care		Practice Environment Scale of the Nursing Work Index
	Quality and quantity of nursing documentation		Modified D-Catch Tool
	Confidence in communication		Confidence with communication survey
Patients/Carers	Satisfaction with nursing care		Schmidt's Perceptions of Nursing Care Survey
	Experience		Australian Hospital Patient Experience Question Set
Medical and Allied Health staff	Satisfaction with communication and handover		Satisfaction with communication survey
Patients	Health data		Patient health records
	Satisfaction with nursing care		Schmidt's Perceptions of Nursing Care Survey
	Experience		Australian Hospital Patient Experience Question Set
Nurse facilitators	Implementation fidelity		Implementation fidelity survey

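### Model covariates are to be chosen from unclustered descriptive tests on the trial data, a rule that does not secure calendar period and does not exclude variables the intervention could change

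*Protocol article*

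**What the plan says.** The only model term that the article fixes by name, in the Phase 3 statistical methods under the heading on effectiveness and clinical outcomes, is a random effect for cluster. The other adjustment is set by a rule: the model will "adjust for relevant confounders, identified in the descriptive analyses, as fixed effects".

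The same paragraph says what the descriptive analyses are. It opens with "Survey and health record data collected for implementation evaluation will be analysed using descriptive statistics" and continues "Descriptive statistics will be calculated using the chi-square test for categorical variables", with a t-test or Mann-Whitney test for continuous variables. It ends with "the alpha set to < 0.05". The footnote to Table 3 adds between-cluster tests: "Cluster comparisons—ANOVA for continuous variables", and Pearson chi-square for categorical variables. Table 3 attaches this descriptive approach to every listed outcome. None of these tests is described as allowing for clustering.

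The data cover both conditions; the Data collection section says "Several outcome measures will be collected from a variety of data sources during the control and intervention periods".

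**The concern.** The article states a way of choosing covariates, so this is more than a list left to the analysis plan. An analysis plan that named a fixed set would have to replace this sentence. The method suits this design poorly in four ways.

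- **Routine admission data.** The tests are very sensitive and ignore clustering. They will pick out trivial differences and stable differences in case mix between clusters, and the cluster effect already deals with the latter.
- **Surveys and record sub-samples.** The same tests have little power and can pass over imbalances that matter.
- **Calendar period.** In a stepped wedge, exposure is confounded with time by construction. Period is not a patient characteristic, so comparing patient characteristics is not a reliable way to bring it into the model.
- **Variables on the causal path.** The wording does not confine candidates to variables that the intervention cannot change.

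At stake is bias in the effect estimate, either from a secular trend left unadjusted or from adjusting away part of the effect.

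**Working it through.** **Inputs.** Table 2: 11,400 + 12,861 + 13,367 + 10,981 = 48,609 admissions a year. Study setting: 4050 admissions a month. Fig. 3 caption: control 3 to 12 months, transition 3 months, intervention 3 to 12 months. Trial status: 1 July 2026 to about 31 December 2027, which is 18 months. Sample size section: "an assumed intra-class correlation of 3%, 5% significance (two-tailed) and 80% power".

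**1. Reproduce the stated volume.** 48,609/12 = 4050.75, which agrees with 4050.

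**2. Admissions per condition.** Read the caption as 3/6/9/12 control months and 12/9/6/3 intervention months. Each condition then has 30 cluster-months. With equal clusters, n = 30 × 4050/4 = 30,375. With the Table 2 volumes the figure runs from 29,303 to 31,458, depending on the order of the clusters.

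**3. Smallest difference an unclustered test calls significant at 0.05.** The formula is 1.96 × √(2p(1−p)/n).

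| Prevalence p | Difference (percentage points) |
|---|---|
| 5% | 0.35 |
| 20% | 0.64 |
| 30% | 0.73 |
| 50% | 0.80 |

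**4. A gap produced by the schedule alone.** Assume a characteristic at 60% in the first-sequence cluster and 50% in the others, constant over time. That cluster supplies 3/30 of control time and 12/30 of intervention time.

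- Control: 50 + 10 × 3/30 = 51%.
- Intervention: 50 + 10 × 12/30 = 54%.

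The 3.0-point gap is 3.0/0.80 = 3.75 times the threshold, although nothing has changed.

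**5. How often an irrelevant covariate is flagged.** Simulation with 2000 runs per setting: a binary covariate at 30%, varying by cluster, unrelated to intervention or time, with random sequence order.

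| ICC of covariate | Control vs intervention | Across clusters |
|---|---|---|
| 0 | 4.9% | 4.6% |
| 0.001 | 32% | 92% |
| 0.005 | 63% | 99% |
| 0.01 | 74% | 99.7% |
| 0.03 | 84% | 99.9% |

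The article gives 0.03 as its sample-size assumption, not as a value for covariates, so the range is what matters.

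**6. Smaller samples.** Assume 200 to 630 respondents per condition. Power to detect 30% against 32% is 6% to 12%. For an imbalance of 0.1 SD it is 17% to 43%. An imbalance of 0.16 to 0.28 SD is needed for 80% power.

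**7. Calendar time.** Take a cluster with c control months, 3 transition months and 15 − c intervention months. The control midpoint is c/2 and the intervention midpoint is c + 3 + (15 − c)/2. The distance between them is 3 + 7.5 = 10.5 months, whatever c is. Suppose a model has a cluster effect but no period term, and the intervention does nothing. A background decline of 2%, 5% or 10% a year (assumed) would then appear as a rate ratio of about 0.98, 0.96 or 0.91, from (1 − decline)^(10.5/12). H2 targets a 10% reduction.

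**8. Adjusting for something the intervention changes (illustration).** Suppose such a variable carried 25%, 50% or 75% of the log effect. A true rate ratio of 0.80 would then be estimated as 0.80^0.75 = 0.85, 0.80^0.50 = 0.89 or 0.80^0.25 = 0.95. The shares are assumed.

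**The case against.** **Error rate.** A reader might infer that choosing covariates by test makes the nominal 5% level unreliable. The check made here does not support that for pre-admission covariates. It simulated 60,740 admissions in four clusters with ten covariates at ICC 0.03, five of them prognostic, and no intervention effect or trend. Tests selected 84% of the covariates. A linear probability model with cluster effects rejected in 5.75% of runs with selection and 5.25% with the full fixed set (Monte Carlo standard error about 1.1 points). The SD of the estimate was 0.0032 against 0.0031. A repeat of 1000 runs gave 5.6% and 5.7%. The selection tests use covariates and condition, not outcomes, and a rule that admits most candidates is close to full adjustment. This stands.

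**The threshold.** The article does not say that every variable with p<0.05 enters the model, and the word for relevance leaves room for judgement. It also introduces the descriptive tests for data gathered to evaluate implementation, so their use on all admissions is an inference. This stands as a limit on steps 3 to 5.

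**Flagging nearly everything.** This holds at most for admission-level data. Table 4, with the planned sample sizes, is not shown, and H4 and H5 rest on surveys or record sub-samples.

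**Timing.** A reader might infer that the adjustment stays open until outcomes have been seen. The article is silent on when selection happens, and the analysis plan may settle it.

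**Causal path.** A variable changed by the intervention is not a confounder, and nothing suggests the sponsor means to adjust for one. The wording lacks a safeguard; it does not plan the error.

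**Calendar period.** Its place in the model is a wider question of specification, and the analysis plan may name it. The point here is narrower: the stated rule does not secure it.

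**Conclusion.** The point holds as a weakness of the stated rule. For H1 to H3, unclustered tests would respond to differences of 0.35 to 0.80 points and mainly to stable cluster differences. For surveys and record sub-samples they could miss real imbalances. The rule neither guarantees calendar period nor excludes variables the intervention could affect. Of these gaps, calendar period has the clearest potential for bias, because the two conditions lie 10.5 months apart within every cluster.

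The admission figures assume that all admissions are analysed, on a 3/6/9/12 split with a 0.05 cut-off. The 10.5 months needs only the 18-month window and 3-month transition. The trend and mediation figures are illustrations. The change should be made; nothing here shows that the planned analysis would be invalid.

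**What to change.** Replace the sentence with an adjustment set fixed before outcome data are examined:

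- calendar period in every model;
- for patient outcomes, ward type and pre-admission characteristics available in the record, such as age;
- for staff-survey outcomes, staff characteristics the nurse survey already collects (position, experience), and the equivalent for medical and allied health staff where it is recorded.

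State that no covariate is selected by significance test and that none the intervention could affect is included. The criterion is whether the intervention could change the variable, not whether it was recorded after rollout, since every intervention-period patient is recorded after rollout. Keep the descriptive tables for description, and label any later addition a sensitivity analysis.

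The cost is a few lines of text, and recruitment is not due to start until July 2026. Age, ward type and nurse position and experience are mentioned in the article; any further candidate, such as emergency or planned admission, should first be confirmed as available. The price is less freedom to add covariates to the main model later.

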**Methods:**

HIRAID® will be adapted for the hospital inpatient setting using a real-time Delphi technique and co-design with frontline hospital inpatient nurses, consumers, managers, physicians and allied health clinicians (Phase 1). An explanatory mixed methods study incorporating staff surveys and focus groups, informed by behaviour change theory, will be used to generate the implementation strategy (Phase 2).

The intervention will be trialled with 1259 nurses from 35 inpatient wards (10 hospitals) across three health services in two Australian states, using a Type II hybrid effectiveness-implementation design, including a Stepped-Wedge clustered Randomised Control Trial (Phase 3). There will be four clusters, determined by geography and clinical governance, where 4050 patients are admitted per month. These clusters were selected due to their direct admission of acutely unwell patients that are at a high risk of experiencing adverse events.

Routinely collected data, guidance documents, and pre- and post-intervention surveys of patients, carers, nursing and medical staff will be used to test the seven study hypotheses. Sample size calculations were based on prior research, assuming a 3% intra-class correlation, 5% significance (two-tailed) and 80% power, and using Woertman’s Stepped-Wedge estimate approach. Evaluation of implementation and fidelity will be assessed using the RE-AIM framework. Outcomes of interest include rates of preventable nurse-associated clinical deterioration, hospital-acquired complications, patient and carer experiences with care, and quality of nursing documentation and communication.

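### Four randomised clusters, one cluster random effect and a 0.05 test: for the event-rate outcomes the error rate holds only if clusters share the same time course, and no small-sample reference is fixed

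*Protocol article*

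**What the plan says.** The unit of randomisation is clear in three places. The abstract states "There will be four clusters, determined by geography and clinical governance". The Phase 3 study design section states "Four clusters will be progressed through three sequential phases". The randomisation section states "Each cluster will be randomly allocated to one of four starting dates for implementation". The study design section also uses the word for a single ward, "Each participating hospital ward (cluster) will begin in the control phase", although wards are not randomised individually.

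The analysis is described under Statistical methods, HIRAID effectiveness/clinical outcomes. It names logistic, Poisson or negative binomial mixed models, and on dependence it says "The model will account for the random effect of the cluster and will adjust for relevant confounders". The software is SPSS, with "alpha set to < 0.05". Table 3 assigns this family of models to outcomes 1-6, which belong to H1-H3. The section names no calendar-time effect, no variation between quarters within a cluster, and no reference distribution for the test. The sample size section works with "an assumed intra-class correlation of 3%, 5% significance (two-tailed) and 80% power".

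**The concern.** A single cluster random effect treats each cluster's level as constant, apart from whatever fixed effects are added. With thousands of admissions per cluster-quarter, any real drift particular to one cluster is then counted as treatment signal, or as error far smaller than it is. Some drift is plausible here: the clusters span three health services in two states, and the study plan section allows other initiatives to run alongside and asks only that they be documented.

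The usual repair is an extra variance term. With four clusters that term is estimated from very few cells, so a 1.96 cut-off is then too lenient. A plan that makes only the first repair would still overstate the evidence. At stake are the 5% level and the 95% intervals for deterioration calls, hospital-acquired complications and harm events.

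**Working it through.** **Layout.** The Fig. 3 caption gives 3-12 months control, 3 months transition and 3-12 months intervention. Trial status gives July 2026 to December 2027, which is 18 months or 6 quarters. I read this as 4 clusters x 6 quarters = 24 cells. Dropping 4 transition cells leaves 20.

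**Degrees of freedom.** 20 cells - 6 quarter effects - 3 cluster contrasts - 1 treatment effect = 10.

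**Volume.** Study setting: 4,050 admissions a month, so 4,050 x 3 / 4 = 3,037.5 per cluster-quarter.

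**Events per cell (assumed 53-400).** Low end: the mean of Table 2's infection rates is (3.22 + 2.34 + 2.35 + 3.33)/4 = 2.81 per 1000. Taking this as per 1000 patient days, with full occupancy and equal clusters, 834/4 beds x 91 days x 2.81/1000 = 53. High end: 400 is an assumption, equal to 400/3,037.5 = 132 per 1000 admissions. Harm Score 3 falls between: 1,829/16 = 114. The SD of the four Table 2 rates is 0.54, and 0.54/2.81 = 19%, used as the between-cluster SD.

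**The plan's own figure.** P(|Z| > 1.96) = 0.05. When the data match the stated model (constant cluster effects), simulation with quarter effects included gave 3.9-4.5% in a linear mixed model. A Poisson mixed model gave 6.3% and 7.7% (300 runs each, Monte Carlo SE about 1.5 points). This is near nominal.

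**Model as written, with cluster-quarter variation present.** If the log rate of a cell has extra SD s and the cell has m events, the true variance exceeds the modelled variance by about 1 + m s². The rejection rate is P(|Z| > 1.96/√(1 + m s²)).

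| m | s | 1 + m s² | cut-off on the true scale | rejects |
|---|---|---|---|---|
| 53 | 0.05 | 1.13 | 1.84 | 6.6% |
| 150 | 0.10 | 2.50 | 1.24 | 21.5% |
| 400 | 0.15 | 10.0 | 0.62 | 53.5% |

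This agrees with the simulated range of about 7-55%.

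A second route uses the protocol's ICC of 0.03 in a linear model and assumes cluster autocorrelation (CAC) of 0.95 or 0.8:
- CAC 0.95: 1 + 3,037.5 x 0.03 x 0.05/0.97 = 5.70, and 1.96/√5.70 = 0.82, giving 41%. Simulated: 41%.
- CAC 0.8: 1 + 3,037.5 x 0.03 x 0.2/0.97 = 19.8, and 1.96/√19.8 = 0.44, giving 66%. Simulated: 65%.

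Replacing 1.96 by t on 10 df in this same model still rejects 34.6% and 60.3%. Changing the reference alone repairs little.

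**Variation modelled, cut-off still 1.96.**
- Unbiased variance: P(|t10| > 1.96) = 7.8%. Mixed-model simulations with REML gave 5.7-9.7%. The overall range with REML-type variance is about 6-11%.
- Maximum likelihood divides by 20 instead of 10, so the cut-off is effectively 1.96 x √(10/20) = 1.39 and P(|t10| > 1.39) is about 19.6%. Mixed-model simulations gave 8.5-17.6%. The overall range is about 9-19%.

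**Both repaired.** A cell-level regression with cluster and quarter effects and t on 10 df rejected 4.9-5.1% in all 12 settings (53, 150 or 400 events; SD 0, 5, 10 or 15%; 20,000 runs each). REML with a cluster-period term and t10 gave 4.7% (CAC 0.95) and 5.5% (CAC 0.8). Maximum likelihood with t10 still gave 11.7-12.0%, so the estimation method matters too.

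**Cost and permutation limit.** 2.228/1.960 = 1.14, so intervals are about 14% wider. There are 4! = 24 orders, so the smallest permutation p-value is 1/24 = 0.042.

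**The case against.** The strongest reply is that this rests on silence. The article states no reference distribution or estimation method, so a normal reference is an inference, and degrees-of-freedom detail is often left to an analysis plan. That stands as far as the choice of method goes. It does not cover the random-effects structure, which the article does state, together with the software and the alpha level.

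A reader might infer that four clusters inflate the error rate whichever variance terms are used. The documents do not support this: with constant cluster effects the stated model is near 5%. A reader might also take 15-19% as the general size. Those figures need maximum likelihood, which the plan does not specify. Nor can the finding be carried to H4-H5. Table 3 lists linear, logistic or multiple linear regression for those survey and documentation scores, and the checks covered event rates only.

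Two further limits are fair. The cluster-quarter SDs, the autocorrelations and the upper event count are assumptions, and the 19% between-cluster SD comes from infection rates. A negative binomial model fitted to cluster-quarter totals would absorb much of the extra variation, leaving only the reference distribution at issue. Fitted to individual admissions it would not, because its dispersion is not shared within a cluster-quarter.

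**Conclusion.** The concern holds for the event-rate outcomes (H1-H3) in a conditional form. The stated model is valid at 5% only if no cluster changes over time differently from the others. With a cluster-quarter SD of 5-15% and 53-400 events per cell it rejects about 7-55% of true nulls. Modelling that variation while keeping a normal reference leaves about 6-11% with REML-type variance and about 9-19% with maximum likelihood. The variance structure and the reference distribution therefore have to be fixed together.

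These sizes rest on the 20-cell reading of the wedge, on quarter effects being in the model, and on the assumed variation. They do not describe Harm Score 1, the main H3 measure: 14 events in 2023 is 14/16 = 0.9 per cluster-quarter, where 1 + 0.9 x 0.15² = 1.02, so extra variation hardly matters and sparseness is the difficulty instead.

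**What to change.** In the statistical methods section, for H1-H3, state that the model includes quarter effects and cluster-by-quarter variation, and that the treatment effect is tested with a small-sample reference. Two routes would serve:

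- a regression on cluster-quarter rates with cluster and quarter effects and t on about 10 df; or
- REML-type estimation with Satterthwaite or Kenward-Roger degrees of freedom.

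Take the confidence intervals from the same distribution. Say how Harm Score 1 will be handled, since a log-rate regression is not workable with many empty cells.

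State that cluster in the model means the four randomised groups, and reconcile the sentence that calls a ward a cluster. Acknowledge the four-unit limit in the study design section or under methodological considerations and risks. A 24-order permutation p-value is optional as a sensitivity analysis; it falls below 0.05 only if the observed order is the single most extreme.

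The cost is a few sentences, intervals about 14% wider and somewhat lower power. Data collection does not change, and the planned start of recruitment in July 2026 is not affected.
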